#### Data Analysis Plan

The primary research question for specific aim 1 was to identify patient characteristics associated with UPOU. A case-control design was used with controls time matched to cases. The expectation was that multiple patient characteristics would be associated with UPOU. Descriptive statistics (means, medians, and ranges) were generated to compare cases and controls on all patient characteristics. Differences in patient characteristics between cases and controls were assessed using bivariate tests including the McNemar test for categorical variables and paired 2-tailed *t* tests (or Wilcoxon signed rank test, if needed) for continuous variables. The results of the bivariate analyses were used to select variables for conditional logistic regression analyses to regress UPOU on all variables identified as potentially associated with the UPOU. The regression models were constructed in stages by incorporating predictors in conceptual blocks and using standard selection methods to retain variables. All models included a fixed effect for site. ORs and 95% CI were used to evaluate the magnitude and statistical significance of the association between predictors and outcome.

### Specific Aim 2

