#### Sample Size Estimates

Based on our preliminary work [3,9,57-62], we estimated the rate of episodic opioid use would be 20% and the estimated rate of long-term use would be 7%. This would yield approximately 200 (780 × .27 = 210.6) patients developing some form of UPOU at each site. The analysis for specific aim 1 involved examining a wide variety of predictors of UPOU rather than 1 specific exposure. As a result, the minimum detectable odds ratios across a range of sample sizes were calculated. Setting the power at 0.8 and α at .05 (2-tailed), a total sample size of 1200 (600 cases and 600 controls) allowed detection of an odds ratio of 1.38 with a predictor that had a prevalence of 0.5 in controls and zero correlation in exposure between cases and controls. The detectable odds ratio (OR) goes up as the correlation between cases and controls becomes positive (detectable OR=1.48 with *r*=0.3), and it also increases as the prevalence of the exposure in the control group increases (detectable OR=1.55 with *r*=0.3 and prevalence of exposure=0.7 in controls).

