#### Data Analysis Plan

The primary research question for specific aim 2 was to identify clinician and practice environmental characteristics associated with UPOU. The analysis plan was similar to the plan described for specific aim 1. Descriptive statistics (means, medians, and ranges) were generated to compare cases and controls on all clinician and practice environmental characteristics. Differences in clinician characteristics between cases and controls were assessed using bivariate tests including the McNemar test for categorical variables and paired 2-tailed *t* tests (or Wilcoxon signed rank test, if needed) for continuous variables. The results of the bivariate analyses were used to select variables for conditional logistic regression analyses to regress UPOU on all variables identified as potentially associated with UPOU. The regression models were constructed in stages by incorporating predictors in conceptual blocks and using standard selection methods to retain variables. All models included a fixed effect for site. ORs and 95% CI were used to evaluate the significance of the associations between predictors and outcome.

### Specific Aim 3

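### Predictors are screened, retained and tested on the same data, with no stated allowance for selection or multiplicity: weak odds ratios are inflated and false predictors are likely

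*Protocol article*

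**What the plan says.** The Aim 1 Data Analysis Plan sets out one sequence on one data set.

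- Cases and controls are compared by "bivariate tests including the McNemar test for categorical variables and paired 2-tailed *t* tests" or Wilcoxon tests, and "The results of the bivariate analyses were used to select variables for conditional logistic regression analyses".
- Models are then built by "incorporating predictors in conceptual blocks and using standard selection methods to retain variables".
- Finally, "ORs and 95% CI were used to evaluate the magnitude and statistical significance of the association between predictors and outcome".

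The Aim 2 Data Analysis Plan repeats this for clinician and practice characteristics, again "using standard selection methods to retain variables".

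Under Sample Size Estimates, Aim 1 is described as "examining a wide variety of predictors of UPOU rather than 1 specific exposure", with two-sided alpha .05. Neither plan states a screening or retention threshold or the number of candidates. Neither mentions data splitting, resampling, shrinkage, multiplicity control or an exploratory label for the intervals.

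**The concern.** The same outcome data choose the predictors and then judge them. A nominal 95% CI assumes that the model was fixed before the data were seen. After selection, a weak predictor appears in the final model mainly when chance has pushed its estimate away from 1, so its reported odds ratio is too large. If retention needs p<.05, a null predictor that is retained has a CI excluding 1 by construction, so reading that interval as evidence is circular. Separately, testing many predictors at .05 each makes some false findings likely whatever route is taken.

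The results are meant to be used. Aim 3 says that the Aim 1 findings fed directly into the patient-domain structural model, which is fitted to the same patients. The claims measures listed under Aim 3 include no heat-pain testing, craving or catastrophizing score, so a false positive on one of those has no stated second check. The Discussion expects prompt effects on clinical care, and the Conclusions foresee record-system alerts.

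**Working it through.** **1. Inputs.** From the protocol: two-sided alpha .05, power 0.8, 600 planned pairs, 513 cases and 517 controls recruited, 148 clinicians surveyed. The number of candidates is not given. A rough count of the Aim 1 assessments is: demographics and history 10, misuse instruments 3, withdrawal 1, craving items 3, pain intensity 1, body map 1, MPI 1, depression and catastrophizing 2, smoking 1, heat pain 1, named concomitant treatments 5. The total is 29, and subscales would add more. The checks therefore assume 15 to 45 candidates.

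**2. The plan's own figure.** For 1:1 matching, with P = ψ/(1+ψ) and discordant proportion p_d:

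pairs = [1.96/2 + 0.842·√(P(1−P))]² / [(P−0.5)²·p_d]

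With control prevalence 0.5 and r = 0, p_d = 0.5.
- ψ = 1.38: P = 0.5798, pairs = 1.9471/(0.006373 × 0.5) = 611.
- ψ = 1.384: P = 0.5805, pairs = 1.9469/(0.006486 × 0.5) = 600.

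The stated 1.38 reproduces, as do 1.48 and 1.55 (recomputed 1.475-1.477 and 1.548-1.559). These figures describe one predictor tested once at .05.

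**3. Pooled coverage after selection.** Matched pairs were simulated with binary predictors of prevalence 0.5: two each at OR 1.2, 1.38 and 2.0, the rest null. Selection was a McNemar screen at .05 or .20, then backward elimination in conditional logistic regression at .05 or .10 (400-600 runs per setting, 513 or 600 pairs). All thresholds and effects are assumptions.

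| Candidates | Pooled CI coverage, retained set | Null share of retained set | Any falsely significant predictor |
|---|---|---|---|
| 15 | 83% | 10% | 36% |
| 30 | 72-78% | 18-35% | 58-72% |
| 45 | 63% | 33% | 83% |

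The same model without selection covered 94-95%.

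One setting shows where the shortfall lies (513 pairs, 30 candidates, no correlation, screen .20, retention .05):
- Null: 24 × 0.05 = 1.20 retained, 0 covered.
- OR 1.20: 2 × 0.29 = 0.58 retained, × 0.891 = 0.52 covered.
- OR 1.38: 2 × 0.67 = 1.34 retained, × 0.950 = 1.27 covered.
- OR 2.0: 2 × 1.00 = 2.00 retained, × 0.940 = 1.88 covered.

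Pooled: 3.67/5.12 = 72%. True predictors only: 3.67/3.92 = 94%. Almost all of the loss comes from retained nulls. With retention at .10, retained nulls were covered 43-47% of the time.

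**4. Inflation.** Across the settings in step 3:
- True OR 1.20: average reported 1.36-1.47, coverage 0.86-0.93.
- True OR 1.38: average reported 1.44-1.54, coverage 0.93-0.97. On the log scale, ln 1.44/ln 1.38 = 1.13 and ln 1.54/ln 1.38 = 1.34, so 13-34% too large.
- True OR 2.0: average reported 2.01-2.07, coverage 0.93-0.96.

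Further simulations with 30-40 candidates and eight true effects of OR 1.2 per SD gave log ORs 24-31% too large and pooled coverage of 73-83%. At OR 1.5 per SD the inflation was 2-7%. The scales agree: a binary predictor of prevalence 0.5 has SD 0.5, so OR 1.38 corresponds to 1.38^0.5 = 1.17 per SD.

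**5. Multiplicity.** With m independent null predictors tested at .05, P(any false positive) = 1 − 0.95^m.
- 15 candidates, 9 null: 0.37 (simulated 0.36).
- 30 candidates, 24 null: 0.71 (simulated 0.58-0.72).
- 45 candidates, 39 null: 0.86 (simulated 0.83).
- 40 candidates, all null: 0.87 (simulated 0.86).

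The formula contains no selection step, yet it gives nearly the simulated values.

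**6. Same data, selection removed.** With 513 pairs and 40 candidates, all null, at least one false positive occurred in 84% of runs with screening and retention (mean 1.5 per run) and in 89% with the full model (mean 2.2). With eight effects of OR 1.2 per SD the figures were 80% and 85%. Over 30-40 candidates the ranges were 67-86% with selection and 68-87% without. False discovery rate control brought this down to 17-20%.

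**The case against.** The strongest reply has four parts.

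- **The aim is exploratory.** The plan says "The primary research question for specific aim 1 was to identify patient characteristics associated with UPOU", and secondary work in claims data is planned. This softens the point but does not remove it: the plan reads the intervals as tests of significance, and the claims step compares structural models rather than correcting the Aim 1 intervals.
- **Details may sit in an unseen analysis plan.** Thresholds and corrections often do, and their absence here is not the complaint. The complaint is the stated sequence. It is also fair that the text names no particular selection algorithm and that every threshold and candidate count above is assumed.
- **Strong predictors are unaffected.** This stands. A reader might infer that the intervals of all retained predictors are wrong or too narrow. The check does not support that: retained true predictors have near-nominal coverage overall, and effects near OR 2 are almost unbiased.
- **Selection does not create the false predictors.** This also stands. A reader might infer that dropping the screen would remove them. Step 6 shows that it would not; only multiplicity control does.

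Bootstrap optimism correction is no remedy for the intervals either. It mainly addresses model performance and does not give valid CIs for selected odds ratios.

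**Conclusion.** The concern holds in two separate parts.

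1. **Selection.** It inflates the reported odds ratios of weak true predictors and makes the significance of a retained null predictor circular. The low pooled coverage comes mostly from those nulls. At the design OR of 1.38, coverage holds but the estimate is inflated.
2. **Multiplicity.** The false-positive risk of roughly 36-86% should be attributed to the number of tests and not to the selection route.

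Direction and mechanism follow from the stated sequence. The sizes rest on the assumed candidate counts, cut-offs and effects, and should be read as ranges. The protocol's detectable odds ratios are not in question. The calculations model Aim 1. Aim 2 follows the same sequence with 148 clinicians against the 410 to 760 anticipated; no separate figure was computed for it, and an unselected full model has not been shown to be feasible there.

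**What to change.** **Aim 1.** Drop the bivariate screen. Enter all candidates by conceptual block in a conditional logistic model without p-value selection, take ORs and CIs from that model, and control the false discovery rate across candidates. With 513 cases, 30 to 40 parameters leave 513/40 = 13 to 513/30 = 17 cases per parameter; multi-category variables would lower this.

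**Aim 2.** Use a short list of predictors chosen from the conceptual framework and not from bivariate p-values, or a penalised model, and label the estimates exploratory.

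**Both.** Label the ORs and CIs of any reduced model still reported as exploratory and unadjusted for selection.

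**Cost.** The protocol says that the Aim 1 and Aim 2 analyses are complete and the manuscripts are in preparation, so this means re-analysis of existing data. No new data are needed. Intervals will be wider and fewer predictors will be called significant.

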#### Overview

Clinicians prescribing opioids to patients in specific aim 1 were recruited for assessment of prescribing characteristics.

#### Clinician Recruitment

Clinician recruitment was site specific, but a similar stepped approach was used. First, an email message was sent to each clinician briefly explaining that they had issued an opioid prescription to a patient participating in the observational study. The email note contained a link to a validated self-report survey regarding clinician attitudes and beliefs about opioids, and clinicians were asked to complete the survey [6]. Clinicians who did not respond were sent a reminder email 1 week later. Clinicians who did not respond to the reminder email after an additional 1-week period were sent a final email. After a 2-week period, all clinicians not responding to the email messages were sent a paper version of the survey using each site’s intracampus mail system. Clinicians not responding to the mailed survey after a 4-week period were considered nonresponders.

#### Study Assessment

Clinicians were assessed using the Clinicians’ Attitudes and Beliefs About Opioids Survey (CAOS) [6]. The validity and test-retest reliability of the CAOS has been reported [6]. The CAOS also assesses clinician demographics and practice characteristics including sex, age, years in practice, professional training (physician surgeon, nonsurgeon physician, nurse practitioner, and physician’s assistant), organization of practice (single specialty, partnership, solo, or multispecialty), practice structure (academic or university versus clinic or hospital based), proportion of weekly patient appointments involving management of chronic pain, and proportion of patients with chronic noncancer pain currently receiving opioids.

#### Sample Size Estimates

There was no information available to predict how many unique clinicians prescribe opioids to patients in aim 1. A 2013 meta-analysis of provider surveys estimated a survey response rate among health professionals of 53% [63]. Thus, we conservatively estimated the response rate would be between 35% to 65% and anticipated between 410 and 760 clinicians would complete the survey.

#### Data Analysis Plan

The primary research question for specific aim 2 was to identify clinician and practice environmental characteristics associated with UPOU. The analysis plan was similar to the plan described for specific aim 1. Descriptive statistics (means, medians, and ranges) were generated to compare cases and controls on all clinician and practice environmental characteristics. Differences in clinician characteristics between cases and controls were assessed using bivariate tests including the McNemar test for categorical variables and paired 2-tailed *t* tests (or Wilcoxon signed rank test, if needed) for continuous variables. The results of the bivariate analyses were used to select variables for conditional logistic regression analyses to regress UPOU on all variables identified as potentially associated with UPOU. The regression models were constructed in stages by incorporating predictors in conceptual blocks and using standard selection methods to retain variables. All models included a fixed effect for site. ORs and 95% CI were used to evaluate the significance of the associations between predictors and outcome.

### Specific Aim 3

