#### SEM Analysis

The primary goal of aim 3 was to combine the results from aims 1 and 2 and extend these by building a statistical model that synergistically integrated the three domains of the UPOU conceptual framework. The UPOU framework has a number of complexities that limit the use of regression including multiple correlated predictors and outcomes, unobserved constructs that are difficult to directly measure, and nesting of patients with clinicians who are nested within sites. SEM can estimate latent variables and include them as both exogenous and endogenous variables in the same model, use multiple observable and quantifiable indicators to estimate latent variables from the shared variability of these indicators, and accommodate multiple endogenous variables (ie, dependent variables or outcomes) in 1 model. Multilevel SEM can estimate latent variables at 1 or more levels (eg, patient and clinician levels) and appropriately test associations at and across these different levels for categorical and continuous outcomes.

The SEMs were developed in several steps. The number of measurement models were estimated for all constructs that potentially used latent variables. Descriptive statistics were examined including means, medians, SDs, ranges, measures of central tendencies, and normality of the distributions. Extensive preliminary analyses were conducted to evaluate possible inconsistencies in the data, outliers, and variations in the data, and clinically and statistically relevant cutoff points that may facilitate the analyses were identified. The primary outcome measure was UPOU, measured as a dichotomous variable of cases and time-matched controls. The predictors of interest were grouped into 3 domains: patient characteristics, practice environment, and clinician characteristics. Each of these domains contained a number of directly observable and directly unobservable constructs. Examples of directly observable variables in the patient characteristic domain included age, sex, and employment status. Examples of directly unobservable constructs in the patient characteristic domain included symptoms of opioid withdrawal, opioid craving, and the psychosocial impact of chronic pain. Analyses (eg, coefficient α, principal components analysis, and factor analysis) were conducted to determine how to optimally combine scale items into reliable measures.

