#### Clinician Recruitment

A total of 148 clinicians completed the CAOS survey. The Mayo Clinic site recruited 146 (98.6%) clinicians, and 2 (1.4%) clinicians were recruited at the University of Michigan site. Recruitment of unique clinicians at the Mayo Clinic site was limited, in part, by clinicians who prescribed opioids to more than 1 patient. Due to unanticipated administrative barriers at Yale University, no clinicians were recruited at this site. The data analysis of clinician characteristics associated with UPOU has been completed and the manuscript is under active development.

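### Aim 2 applies matched-pair tests to clinician survey data, so a pair counts only if both clinicians responded, and shared clinicians are ignored

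*Protocol article*

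**What the plan says.** The Aim 2 Data Analysis Plan takes its methods from Aim 1: "The analysis plan was similar to the plan described for specific aim 1". It then names them. "Differences in clinician characteristics between cases and controls were assessed using bivariate tests including the McNemar test for categorical variables", and paired t or signed-rank tests serve for continuous variables. The bivariate results choose variables for "conditional logistic regression analyses to regress UPOU on all variables identified as potentially associated with UPOU". The pairs are those of Aim 1: patients still using opioids at day 90, each matched 1:1 to a short-term user on initial issue date within two weeks (Timeline for Establishing CONSORT Criteria).

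On response, the Aim 2 Sample Size Estimates say "we conservatively estimated the response rate would be between 35% to 65" percent, which the article converts to 410 to 760 completed surveys. The Results report 148 completed surveys: 146 at Mayo, 2 at Michigan, none at Yale. They attribute the limited number of unique clinicians at Mayo partly to "clinicians who prescribed opioids to more than 1 patient". The SEM Analysis section of Aim 3 lists "nesting of patients with clinicians who are nested within sites" among the features that limit the use of regression.

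**The concern.** A matched-pair test of a patient characteristic needs data on two patients. A matched-pair test of a clinician characteristic needs two survey responses, one for each patient's prescriber. McNemar and paired tests necessarily lose a pair with one non-responder. The conditional model loses it too unless values are imputed, and imputation is described only for the SEM. Patients whose clinician did answer are discarded because the other member's clinician did not.

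Secondly, the tests assume independent pairs. A clinician who appears in several pairs contributes the same survey values to each, and that clinician's patients may share an outcome tendency. The article recognises this nesting for Aim 3, but the Aim 2 plan has no clustering term, random effect or robust variance. A pair whose two members share one clinician is never discordant and adds nothing.

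The clinician association is Aim 2's primary question and has its own manuscript. The plan therefore risks low power and, with few clinicians, too many false positives, which variable selection would carry into the regression.

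**Working it through.** **Inputs.** From Aim 1 Sample Size Estimates: 600 pairs, two-sided alpha 0.05, power 0.80, control prevalence 0.5, r = 0, detectable OR 1.38. From Aim 2 Sample Size Estimates: response 35% to 65%, published rate 53%, 410 to 760 completers. From Results: 148 completers. Assumed: one clinician per patient, and response independent within pairs.

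**Reproducing the plan's figures.**
- 410/0.35 = 1171 and 760/0.65 = 1169, so the implied base is about 1170 clinicians. 1170 × 0.35 = 409.5 and 1170 × 0.65 = 760.5, as stated. The base is inferred; the article does not give it.
- Matched-pair formula: P = OR/(1+OR); discordant pairs = (z₀.₉₇₅/2 + z₀.₈₀·√(P(1−P)))² / (P − 0.5)²; total pairs = discordant pairs / p_d, with p_d = p₀(1−p₁) + p₁(1−p₀), which is 0.5 here. At OR 1.384, P = 0.5805 and (0.980 + 0.415)² / 0.0805² is about 300 discordant pairs, so about 600 pairs. This agrees with the stated 1.38.

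**Usable pairs and data kept.** Pairs = 600 × response²; patients with clinician data = 1200 × response.

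| Response | Usable pairs | Patients in them | Patients with clinician data | Discarded |
|---|---|---|---|---|
| 35% | 73.5 | 147 | 420 | 65% |
| 53% | 168.5 | 337 | 636 | 47% |
| 65% | 253.5 | 507 | 780 | 35% |

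Without independence, usable pairs can range from 0 to 210 at 35% and from 180 to 390 at 65%.

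**Detectable OR.** The same pair formula gives 2.62 at 73.5 pairs, 1.86 at 168.5 and 1.65 at 253.5. Check at 2.62: P = 0.724; (0.980 + 0.376)² / 0.224² = 36.7 discordant pairs; divided by 0.5, 73.5. Power for an OR of 1.38 falls from about 79% with 600 pairs to about 16%, 31% and 43%. Keeping all patients with clinician data, the two-proportion formula gives 1.74 with 210 + 210 and 1.50 with 390 + 390. Those unpaired figures make no allowance for clustering.

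**Shared clinicians.** McNemar's test was simulated for a binary clinician trait with no effect (prevalence 0.5), with a clinician-level random effect on UPOU around a 27% rate. The intraclass correlation (ICC) and caseload are not in the documents, so these are assumed ranges.
- Planned scale: 420 to 780 patients over 410 to 760 responders is about one patient per clinician. With 410 to 760 responders, 74 to 254 pairs and ICC 0.05 to 0.10, rejection was about 5% to 7%.
- 148 clinicians, 100 pairs, ICC 0.05 to 0.10: about 6% to 7%.
- 148 clinicians, 300 pairs, skewed caseloads: about 9% to 10% at ICC 0.05 and between 14% and 15% at ICC 0.10. With even caseloads: about 7% and 9%.
- No clinician effect: about 5%, as it should be.

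**The case against.** The strongest reply is that the two harms belong to different scenarios. Pair loss is computed at the planned response, where clinicians are numerous and clustering is slight; material inflation appears only with the 148 obtained, and its size rests on assumed values. That is right, and the two should not be added. Aim 3's multilevel SEM also models nesting and provides for missing data. That limits the defect to Aim 2, but Aim 2 reports its own odds ratios.

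A reader might infer four stronger points that the documents do not support.
- *Most clinician data are lost.* This holds only below 50% response; at 65% the loss is 35%. Responses were concentrated at one site, so response may be positively correlated within pairs, which would reduce the loss.
- *Cases accumulate prescribers, so clinician exposure is biased by construction.* The Aim 2 Overview says only "Clinicians prescribing opioids to patients in specific aim 1 were recruited for assessment of prescribing characteristics". It describes recruitment, not which prescriber's survey is linked to a patient, and a condensed article may leave that rule to the full protocol.
- *The site term does harm.* "All models included a fixed effect for site" is the wording, and a term constant within a pair simply drops out of a conditional model without bias. Matching within site is not stated.
- *The matching has broken down.* Table 1 allows 422 + 13 + 71 = 506 within-site pairs, so as few as 1030 − 1012 = 18 patients need be unmatched.

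**Conclusion.** The point holds for Aim 2 and should be fixed. The stated tests use a pair only when both clinicians responded and make no allowance for shared clinicians. At the plan's own response range, about 74 to 254 of 600 pairs remain and the detectable OR is about 2.6 to 1.65, against 1.74 to 1.50 with all available patients. This rests on independent response, one clinician per patient, prevalence 0.5 and r = 0.

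The direction of the clustering error is anticonservative when clinicians differ in outcome rate. Its size cannot be fixed from the documents: slight at 410 to 760 responders, and roughly 6% to 14% type I error at 148 under assumed ICC 0.05 to 0.10 and 100 to 300 pairs. A reader might conclude that the Aim 2 results are invalid or that Aim 1 shares the fault; neither follows from the article.

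**What to change.** For Aim 2, replace the paired tests and the conditional model, or accompany them, with a patient-level logistic model that uses every patient whose clinician responded. Include a clinician random intercept, or use GEE or robust variance clustered on clinician, and adjust for initial issue date. State one rule linking a patient to a prescriber and apply it identically to cases and controls. Report the number of patients and clinicians contributing and the spread of patients per clinician. Describe the result as essentially a Mayo estimate, since 146 of 148 clinicians are from that site.

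The cost is revised analysis text and a re-run on data already collected. Because the article says the clinician analysis is complete, the added model should be labelled as specified after that analysis. The statistical downside is that calendar time is handled by adjustment instead of pairing. The Aim 1 matching need not change.
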